## Abstract

Objective: To analyse the overall effectiveness and cost-efficiency of a mobile application (APP) as a community health asset (HA) with recommendations and recovery exercises created bearing in mind the main symptoms presented by patients in order to improve their quality of life, as well as other secondary variables, such as the number and severity of ongoing symptoms, physical and cognitive functions, affective state, and sleep quality. Methods: The first step was to design and develop the technologic community resource, the APP, following the steps involved in the process of recommending health assets (RHA). After this, a protocol of a randomised clinical trial for analysing its effectiveness and cost-efficiency as a HA was developed. The participants will be assigned to: (1st) usual treatment by the primary care practitioner (TAU), as a control group; and (2nd) TAU + use of the APP as a HA and adjuvant treatment in their recovery + three motivational interviews (MI), as an interventional group. An evaluation will be carried out at baseline with further assessments three and six months following the end of the intervention. Discussion: Although research and care for these patients are still in their initial stages, it is necessary to equip patients and health care practitioners with tools to assist in their recovery. Furthermore, enhanced motivation can be achieved through telerehabilitation (TR).

## 1. Introduction

Coronavirus (COVID-19), caused by the severe acute respiratory syndrome SARS-CoV-2, has had a serious impact on the whole world and has triggered unprecedented health, social, and economic crises [1]. Most patients infected by SARS-CoV-2 recover in no more than a month depending on the severity of their symptoms [2,3] However, it is believed that irrespective of the severity of symptoms, around 20% of people continue to show or develop multisystemic symptoms after five weeks or more following the acute infection, while 10% continue to display symptoms after twelve weeks, despite receiving negative PCR test results and developing antibodies [4].

In the absence of a clear definition, this new symptomology had been referred to interchangeably as “Long COVID” or “Post-COVID” [5,6,7]. It is in this context that the National Institute for Health and Care Excellence (NICE) states that COVID-19 symptoms can last for 4–12 weeks and that those whose symptoms continue beyond this period and with no alternative diagnosis will be considered to have “Post-COVID syndrome” [8]. In October 2021, the World Health Organisation (WHO) released an official definition of the condition, referring to it as “Post-COVID condition” [9], a condition that occurs in individuals who were previously likely to have been infected (without diagnostic test confirmation) or confirmed to have been infected with SARS-CoV-2. 

The characteristic symptoms of this new condition are confusing, unspecific, and can be ongoing or fluctuate over time [10,11]. The most prevalent symptoms include chronic fatigue, breathlessness, fever, coughing, headaches, chest pain and/or a sore throat, muscle pain, general aches and pains, palpitations, tingling, diarrhoea, rashes, myalgia, brain fog and neurological symptoms, as well as symptoms of depression and anxiety stemming from extreme fatigue and other physical symptoms, among other causes [12,13,14]. There is a higher prevalence among women than men, with the latter making up 20% of diagnoses [15].

There are still many unknown factors (diagnosis, etiology, and disease phenotypes) that are grouped under the umbrella of long COVID-19, and the response to this illness is in its initial stages [13,16]. Therefore, it is necessary to promote research, especially in the field of primary health care (PHC) [17], as it is these health care practitioners who routinely treat long COVID-19 patients. To generate this evidence, a broader outlook should be adopted that does not focus on deficit care models, and patients themselves should be involved through co-production in health and the opportunities presented by citizen science [18]. In this way, citizens can actively contribute to the research by employing their own intellectual effort, knowledge, tools, and resources. 

In the case of health issues, it will allow for the analysis and implementation of more viable interventions based on patients’ experiences, utilising the knowledge of their strengths and challenges they face. They should be included and involved in care planning with a view to co-production in health with contextualised and salutogenic biopsychosocial care models. Consequently, the recognition of patients’ individual, family, and community health assets (HAs) would be valuable. Understanding how these general resilience resources operate and enable greater consistency, would, in turn, allow them to understand, manage, and find purpose in their condition [19]. This project, based on a qualitative study, has taken the insights (practical wisdom) of those who are suffering from ongoing symptoms having contracted COVID-19 into account. Therefore, the needs of this group in their stages of recovery and the possible responses from the health system and especially from PHC have been jointly considered. 

The recommendation of health assets (RHA) or social prescribing (SP) is a tool that can be used in PHC. It complements the biopsychosocial model and allows for the contextualisation of care through a multidisciplinary and intersectoral approach based on health determinants while granting individuals and communities the necessary means to improve and exercise greater control over their wellbeing [20,21,22,23]. HAs can be defined as any factor or resource which enhances the ability of individuals, communities, and populations to maintain and sustain health and wellbeing. Whether at an individual, family, or community level, the common denominator granted by these assets is the strengthening of individuals or groups’ ability to maintain or improve physical, mental, or social health and to deal with stressful situations. HAs could be seen as general resources to overcome inequality and as essential to strengthen knowledge and skills with regard to maintaining good health, boosting morale, and empowering individuals and communities. As a consequence, there would be less vulnerability and dependence on the healthcare system [24,25]. RHA creates formal mechanisms through HAs to provide certain individuals with non-clinical healthcare alternatives. Thus, within the framework of therapy, we can recommend pre-existing non-clinical community resources. 

To implement RHA, it is important to understand the current state of affairs. Following the COVID-19 pandemic, there have been changes made to the use of many clinical and non-clinical resources. Within this context and as an alternative solution to varying requirements, the pandemic has led to increased use of new technologies in diverse settings, including HAs, to ensure efficient communication between practitioners and patients [26,27]. However, this change has been in the works for around a decade, with the promotion of new technology and its increased use among the general population [28]. A clear example of this is the introduction of telerehabilitation (TR): the provision of rehabilitation services through electronic systems using information and communication technology. TR goes beyond hospital settings, helping to evaluate the effectiveness of rehabilitation in everyday activities [29]. Numerous recent studies looking at different diseases have demonstrated the efficiency of using a mobile application (APP) in the treatment of symptoms [30,31,32]. In addition, using TR for post-COVID patients has been proven to be effective, leading to improvements in dyspnoea, fatigue, and ability [33,34]. To sum up, RHA is a technique used to treat a wide variety of patients, including those diagnosed with long COVID-19. 

Medical rehabilitative treatment options for these patients are still proving to be limited, imprecise, and not entirely effective. However, there are no large-scale studies demonstrating the efficacy of pharmacological treatment and, as such, it is essential to continue working on the rehabilitation options offered to these patients [35]. In addition, scientific evidence suggests that early rehabilitation is essential to regain normal functionality [36,37]. Rehabilitation options similar to those offered to patients with chronic fatigue syndrome have always been indicated, that is, gradual and personalised physical and respiratory exercise therapies led by professionals [38,39]. In addition, as the development of the symptoms has been confirmed, it has become necessary to offer cognitive–behavioural therapy and attention from mental health professionals, given the negative impact of the disease itself on the patient’s quality of life [40,41]. Based on this evidence, it seems necessary to consider all these types of therapies in addition to ensuring healthy lifestyle habits, such as diet or sleep quality, to develop a comprehensive rehabilitation plan for long COVID-19 patients.

In light of this challenge, while co-creating the treatment and rehabilitation process, the need to create a community RHA for this patient group to be implemented at the earliest convenience was identified. This was due to the urgency stemming from the number and variety of symptoms presented by patients, as well as the uncertainty that still exists concerning certain pathophysiological aspects of Long COVID. Given the lack of existing resources for the group concerned, the need to design and develop an APP was raised, called ReCoVery. As far as we know, there are only two projects with a design and with purposes such as the ones presented in this study. However, these other two projects have not yet published their results since they are in the development phase of the clinical trial [42,43]. One of the projects is based on therapies such as those used for patients with fibromyalgia given the shared inability to objectify some symptoms. The two studies will serve as precedents for this project. However, it is considered necessary to design and implement a specific rehabilitation plan for this group of patients, which considers all the effects on their vital areas.

For the reasons outlined above, it would be a community resource, designed through a process of identification and co-creating content with Long COVID patients, who could later use the APP to support their recovery by means of TR. Hence, the objective of this study is to analyse the overall effectiveness and cost-efficiency of an APP as a community HA with recommendations and recovery exercises created bearing in mind the main symptoms presented by patients in order to improve their quality of life, as well as other secondary variables, such as the number and severity of ongoing symptoms, physical and cognitive functions, affective state, and sleep quality. A secondary objective is the analysis of personal factors, such as activation, self-efficacy, or health literacy as mediators of the effectiveness of the treatment.

## 2. Materials and Methods

### 2.1. Methodology to Design and Develop the Community Resource (ReCoVery APP)

This methodology is based on the steps involved in the RHA process.

#### 2.1.1. Start and Contextualisation

Firstly, the project was prepared and contextualised. The main objective was then established as offering rehabilitation through community resources to PHC patients diagnosed with long COVID-19 in the Spanish region of Aragón in order to improve their quality of life, as well as to alleviate their symptoms. To this end, a multidisciplinary team of general practitioners, nurses, psychologists, social workers, physiotherapists, and occupational therapists was created. To contextualise the environment and patient group, a qualitative study was carried out with semi-structured interviews and focus groups in order to identify their needs as well as the resources to be used during the treatment and, particularly, to delve deeper into the identification of community HAs during their recovery.

#### 2.1.2. Identification and Characterisation of Possible Community Activities 

Secondly, after detecting the patients’ lack of knowledge and difficulties due to their specific symptoms in the use or suitability of community resources, the multidisciplinary team was able to identify and characterise usable community activities. A list of activities carried out in the community was created, establishing certain criteria for the selection of activities in order to create a “map of HA for Long COVID patients”. After contacting interlocutors from each resource/activity, it was concluded by consensus that there were no sufficient rehabilitation community resources for this patient group according to the criteria established by the multidisciplinary team. Therefore, the need to create an ad hoc developed resource for this group that was also in line with the needs and demands established in the qualitative study, was considered. As a result, an APP with recovery content was designed and was treated as an HA in itself that, as requested by its users, needed to suit their needs.

#### 2.1.3. Building Community Connection

Thirdly, this phase was dedicated to the process of creation and development of the APP ReCoVery. The iterative method selected for the development of ReCoVery was human-centred design [44,45]. This technique looks to resolve specific problems based on the understanding of the needs and different perspectives of the users themselves as possible recipients of the intervention. In this way, it is possible to promote an adapted and personalised treatment, as well as to ensure adherence to it. For this reason, the initial design of ReCoVery was guided by symptoms, detected needs, and other information that was obtained through individual qualitative interviews and focus group discussions with patients diagnosed with long COVID-19. Subsequently, available scientific evidence was collected on health recommendations and recovery exercises for patients with Long COVID. Within the multidisciplinary team, different work subgroups were created to work on the design and creation of content for each rehabilitation area.

Prior to the start of the intervention, the content of the APP was periodically evaluated both by patients with Long COVID (future users) and by general practitioners, nurses, physiotherapists, occupational therapists, social workers, and psychologists to ensure its suitability and facilitate its adaptation and transfer following the combination between the SCRUM methodology [46] and the agile methodology, with the latter being optimal for software development [47]. In this case, the creation of the APP was distributed in various incremental and interactive development cycles (sprints). At the end of each sprint, the selected patients and the multidisciplinary team had to give their approval or suggest possible modifications that were consensually implemented.

Regarding the architecture of the APP, a native mobile APP with Java language was created through Android Studio, making it compatible with Android, one of the main platforms. Therefore, the APP can be run on all Android smart devices with a software version higher than 5.0. The design of a native APP was chosen, instead of a hybrid one, in order to obtain improved performance in the long term, as well as to be able to make use of the device’s own tools, such as notifications, thus allowing the APP to be kept up to date.

ReCoVery consists of six main modules, as detailed below, each one including a rehabilitation area for long COVID-19 patients, with various options and levels of adaptation being available to meet the specific needs of the patients, as well as self-report registration. In addition, the APP sends periodic reminder notifications, with configuration options.

Regarding the download and use, for new users this APP will not be publicly available, thus guaranteeing that it will only be downloaded onto the intended devices. The APP will be installed on the mobile devices of the participants during the first intervention session, where they will be provided with a username and the personal access password necessary to log in. In the event of having to reinstall the APP, due to a change in device or any other situation, it will be necessary to contact the research staff to make an appointment and carry out the installation process again.

ReCoVery will automatically record usage data, including logins, visits to each module and specific content, time of use, and any other interaction with the APP. In addition, each module consists of daily self-assessments where the self-perception of the users is reported. These data create statistical graphs regarding evolution in the different areas, allowing the user to see their evolution with a time perspective. The answers to these self-assessments will be stored in a SQL server database in the cloud hosted in Azure and will also be locally saved on the patient’s own device in a SQLite database. ReCoVery ensures the privacy and security of user data. In addition to carrying out the download process on-site, an authentication process must be completed for the installation by providing an identification code and a personal password. This information is only requested the first time the patient logs in, meaning that access to the APP will be remotely revoked in the event of loss, theft, or any reported improper use after contacting the research staff. 

With regard to field tests, users will be asked to report any bugs or crashes in the APP, as well as suggest possible modifications for future improvement. Brief individual qualitative interviews will also be conducted to further detail the ideal experience that the patients would prefer to have in relation to the functioning of ReCoVery. The research team will carry out new bibliographic research in order to obtain and incorporate new scientific evidence on the subject. These results were used to identify potential areas for improvement, and an updated version of ReCoVery (V.2.0) will be created.

#### 2.1.4. Recommendation of the APP to Patients

Fourthly, the established protocol for the recommendation of the APP was implemented. To this end, PHC general practitioners in Aragón were asked to identify potential patients who could then be offered the possibility to participate. Following this referral, the evaluating researcher contacted the patients to confirm or decline their participation. They were then invited to the research group’s headquarters for baseline tests, and the APP was recommended to them. This process continued until there was a sufficient sample size, as detailed below. Moreover, means of communication between practitioners and patients were established to monitor the intervention and resolve any arising problems.

#### 2.1.5. Evaluation and Revitalisation

Finally, evaluations could be carried out, in accordance with the previously established parameters, through the users’ contributions and following the quality of health promotion interventions, with the ultimate goal of offering this HA to the whole community. 

Figure 1 shows the flowchart of the APP’s design and development process.

### 2.2. APP’s Validation, Effectiveness and Cost-Efficiency as a HA

#### 2.2.1. Study Design

Randomised ecological clinical trial was represented in two parallel groups. The two interventions to which the patients will be assigned will be: (1st) usual treatment by the primary care practitioner (TAU—control group); and (2nd) TAU + use of the APP as a HA and adjuvant treatment in their recovery, plus three face-to-face motivational interview sessions to enhance adherence (intervention group).

#### 2.2.2. Study Population

The study population will be people with ongoing COVID symptoms who are aged 18 years or over and being treated by PHC. Exclusionary criteria are: diagnosis of a serious uncontrolled illness, which may interfere with the APP recommendations; significant risk of suicide; pregnancy and breastfeeding; participation in another clinical trial within the last six months; existing structured rehabilitative or psychotherapeutic treatment by health professionals and the presence of any medical, psychological or social problem that may significantly interfere with the patient’s participation in the study.

Patients will be recruited by PHC professionals. They will explain the nature of the study and invite patients to participate. Patients from the Association of Long COVID Patients in Aragón will also participate. Recruitment will happen consecutively until the sample size will be reached. 

#### 2.2.3. Sample Size

To calculate the sample size, we will use the data obtained in the study of Dalbosco-Salas et al. [34] because the intervention is similar to ours, and it is developed in PHC, despite being a clinical trial. To the best of our knowledge, to date there are no studies carried out with post-COVID-19 patients that evaluate a similar intervention with a clinical trial methodology. We will use the difference pre-post score of the short-form 36-item questionnaire (SF-36), the value of the possible highest standard deviation (SD), and a minimum expected difference of 19.3 points in the pre-post rating, which were all taken into account. Accepting a risk alpha of 0.05 and a power of 95% in a bilateral contrast, 70 subjects would be required. A maximum loss-to-follow-up rate of 10% has been estimated. The total sample required is 78 subjects, distributed between the two groups (control–intervention).

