To the best of our knowledge, no randomized clinical trials have been performed using TR on Long COVID patients. However, effective studies based on respiratory, physical, or cognitive TR with other groups of patients support the potential viability of this study. As for respiratory TR, two bibliographic reviews of controlled trials of TR for the provision of pulmonary rehabilitation have concluded that TR may be as effective as face-to-face pulmonary/respiratory rehabilitation in individuals suffering from chronic respiratory diseases [128,129]. However, a randomized controlled trial by Cox et al. (2022) concluded that respiratory TR may not be as effective as pulmonary rehabilitation, but it is safe for patients and would have clinically significant benefits [130]. More similar to long COVID-19 patients, a pilot study by González-Gerez et al. (2021) verified that respiratory TR is effective, safe, and feasible for COVID-19 patients having mild-moderate symptoms in the initial stage [131]. Furthermore, the study by Liu et al. (2020) associated respiratory rehabilitation with an improved quality of life in patients infected with COVID-19 [132]. Similarly, the benefits of TR based on physical activity may become comparable with conventional face-to-face rehabilitation approaches while also producing less interference in the patient’s daily life [133]. In this line, the study by Nambi et al. (2021) identified significant improvements in the physical component of the low-intensity aerobic activity group in COVID-19 patients [134]. Additionally, a pilot study by Abodonya et al. (2021) verified a significant improvement in the quality of life of COVID-19 patients who underwent a TR intervention based on physical activity [135]. In addition, prior evidence verifies that TR based on physical exercises may improve the quality of life of groups of patients, such as those suffering from multiple sclerosis [136,137]. Finally, a systematic review has verified that cognitive TR produces benefits in various cognitive domains, such as verbal fluency and executive functions [138]. 

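### The 95% power is tied to a 19.3-point pre-post SF-36 change that appears to stand in for the between-arm difference, with no allowance for improvement under usual care

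*Protocol article*

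**What the plan says.** Section 2.2.3 (Sample Size) takes its planning values from one earlier telerehabilitation study in primary care. The effect is "a minimum expected difference of 19.3 points in the pre-post rating" of the SF-36. The SD is described as the highest possible one, without a number. The result follows: "Accepting a risk alpha of 0.05 and a power of 95% in a bilateral contrast, 70 subjects would be required". Then "A maximum loss-to-follow-up rate of 10% has been estimated", which brings the total to 78, divided between control and intervention.

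The section gives no expected change for the control arm and does not say that 19.3 is a difference between arms. On the evidence available it states that "there are no studies carried out with post-COVID-19 patients that evaluate a similar intervention with a clinical trial methodology". The Discussion (section 4) agrees: "no randomized clinical trials have been performed using TR on Long COVID patients".

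The control arm is not untreated. Section 2.2.6 gives it care under named clinical guidelines. Section 2.2.8 compares the two groups by repeated-measures regression of the SF-36, adjusted for baseline.

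**The concern.** A two-arm trial has to be sized on the difference in change between arms. A pre-post change in a treated group also contains whatever those patients would have gained without the intervention: recovery over time, the effect of ordinary care and any regression to the mean. If 19.3 is such a change, the calculation credits all of it to the app and the motivational sessions, and implicitly sets the mean change under usual care to zero. Calling it a minimum expected difference makes it look like a cautious floor.

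What is at stake is how the result is read. A non-significant result would appear to come from a trial with 95% power, although power against a smaller net benefit could be much lower.

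**Working it through.** **Inputs from section 2.2.3:** two-sided alpha 0.05, power 95%, difference 19.3 points, 70 evaluable, 10% loss, 78 in total.

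**Assumptions:** 1:1 allocation (35 evaluable per arm), an unadjusted two-sample comparison, a gain of exactly 19.3 in the app arm, and usual-care gains of 0, 5 or 10 points. The documents give no usual-care change.

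**1. Loss to follow-up.** 70 / 0.9 = 77.8, rounded up to 78. This reproduces.

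**2. The 70.** The SD is not stated, so the figure cannot be reproduced independently; the SD can only be back-solved.
- Formula: n per arm = 2 × SD² × (1.960 + 1.645)² / 19.3² = 35
- SD = 19.3 × √(35/2) / 3.605 = 22.4 with the normal approximation, or 22.1 with the noncentral t
- Standardised effect: 19.3 / 22.1 = 0.87

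Read as a one-sample or paired calculation, 70 subjects would need SD = 19.3 × √70 / 3.605 = 44.8, a very large value on scales that run from 0 to 100. The two-sample reading, with all 19.3 points as the between-arm difference, fits better.

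**3. Power when usual care improves.** With the normal approximation, the standard error is 22.4 × √(2/35) = 5.355, and power = Φ(difference / 5.355 − 1.960):
- Gain 0, difference 19.3: Φ(3.604 − 1.960) = 95%
- Gain 5, difference 14.3: Φ(2.670 − 1.960) = 76%
- Gain 10, difference 9.3: Φ(1.737 − 1.960) = 41%

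The noncentral t with SD 22.1 gives the same percentages. It also gives 80% power at 15.0 points, 46% at 10 and 15% at 5. Power therefore reaches 80% once usual care gains about 19.3 − 15.0 = 4.3 points.

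**4. Sensitivity to the SD** (noncentral t, 35 per arm):

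| SD | Usual care +0 | +5 | +10 |
|---|---|---|---|
| 20 | 98% | 84% | 48% |
| 22.1 | 95% | 76% | 41% |
| 25 | 89% | 66% | 34% |

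**5. Baseline adjustment.** With an assumed baseline to follow-up correlation r = 0.5, the residual SD is 22.1 × √(1 − r²) = 22.1 × √0.75 = 19.1 if 22.1 is a raw-score SD. If it is a change-score SD, the factor is √((1 + r)/2), which is also √0.75 at r = 0.5. Power becomes about 99% at 19.3, 87% at 14.3 and 52% at 9.3.

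**6. Scale of the shortfall.** Holding SD at 22.4, 95% power would need 2 × 22.4² × 3.605² / 14.3², or 64 per arm (128 / 0.9, or 143 enrolled), if usual care gains 5 points. It would need 151 per arm (302 / 0.9, or 336 enrolled) if usual care gains 10.

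**The case against.** **The within-group reading is inferred.** Section 2.2.3 does not call 19.3 a within-group change. Pre-post change could be the outcome variable and 19.3 the difference between arms in that change, which would be the right input. The section also describes the source study in passing as a clinical trial, and that study was not available for this check. This stands as a limit on certainty. It is the weaker reading, because the next sentence of the same section, and the Discussion, say that no comparable controlled study exists from which a between-arm estimate could come.

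**The plan has some slack.** It uses the highest possible SD, and the analysis adjusts for baseline and uses all follow-ups. A reader might infer that the 95% holds only if usual care does not improve at all. The documents do not support that. If the true SD were 20, power would still be about 95% with a usual-care gain of 2 points (difference 17.3), and at SD 15 it would be 98% with a gain of 5. This stands, although at a gain of 10 even baseline adjustment with r = 0.5 leaves only about 52%.

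**No realistic effect is documented.** A reader might conclude that the trial is underpowered for any realistic controlled effect. The documents give no usual-care trajectory, minimal important difference or plausible net effect for the SF-36, so this cannot be shown. The Introduction's statement that "around 20% of people continue to show or develop multisystemic symptoms after five weeks or more", falling to 10% after twelve weeks, does not fill the gap. It describes symptom persistence among infected people generally, not SF-36 change in enrolled patients with ongoing symptoms.

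**The missing SD.** A journal article may leave this to the full protocol. Its absence is not the point here; it only makes the power figures conditional.

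**Conclusion.** The concern holds as a mismatch between the quantity planned on and the quantity tested. On the article's own account of the evidence, 19.3 points is most probably a change over time, and it is used in a two-arm calculation with nothing set aside for improvement under usual care. The 95% is correct for a net between-arm difference of 19.3 points and overstated for smaller ones.

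Under the stated assumptions, the unadjusted test has about 76% power if usual care gains 5 points (66% to 84% for SD 25 to 20) and 41% if it gains 10 (34% to 48%). Baseline adjustment would recover part of the loss. The true loss cannot be fixed from the documents, because neither the SD nor the usual-care change is given. Type I error, randomisation and the effect estimate are unaffected.

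**What to change.** Keep 78 participants; section 3 reports that 60 are already randomised. In section 2.2.3:

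- Say that 19.3 points is treated as the between-arm difference in SF-36 change and assumes no mean change under usual care. If it is in fact a controlled estimate, say so and give its basis.
- State the SD used and the SF-36 score to which it belongs.
- Restate the power for 70 evaluable participants as 95% for 19.3 points, about 80% for 15 and about 46% for 10, conditional on that SD. Recompute if it is not about 22.
- State that a non-significant result will be interpreted by its confidence interval. With SD 22.1 and 35 per arm, the unadjusted 95% interval has a half-width of about 1.995 × 22.1 × √(2/35) = 10.5 points, so such a result could leave a sizeable benefit open.

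The cost is wording only, with no further patients. The stated power becomes less favourable. The change should be made before results are reported.
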